### Cardiorespiratory monitoring

The CRM for the 20 first participants and for the participants where the home test is showing AHI > 15 (moderate-to-severe sleep apnea) is provided by the Department of Pulmonology, Herlev-Gentofte University Hospital and will quantify the frequency, duration and type of each sleep apnea event (obstructive or central) by measuring AHI, ODI, oximetry distribution and heart rate. Potential treatment for sleep apnea will be at the discretion of the attending sleep apnea physician. Simultaneously with undergoing the CRM, the participants will also be assessed by the NightOwl™ the same night. This simultaneity in the recording by the two different monitoring-methods allows for a direct analysis of the correlation of AHI (and other parameters) measured by CRM and NightOwl™.

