**Methods:**

DAN-APNO is a cross-sectional study at the Department of Cardiology, Herlev-Gentofte Hospital recruiting patients with AF referred to anticoagulation initiation aged 18 to 90 years without known sleep apnea. At least 150 patients will be recruited and undergo medical history, clinical evaluation, several sleep-apnea questionnaires, and a sleep-recording evaluation for four nights with sleep apnea home-monitoring device NightOwl™. Additionally, the first 20 participants and participants with moderate-severe sleep apnea by screening are referred to cardio-respiratory monitoring (CRM). This clinical evaluation allows the comparison of standard evaluation method and the NightOwl™. Clinical measures include Apnea–Hypopnea Index (AHI), Oxygen Desaturation Index (ODI), pulse rate, as well as questionaries about sleep apnea assessment and the clinical feasibility of the NightOwl™ device. Main outcomes comprise analysis of the prevalence and severity of sleep apnea, and clinical and demographic predictors of moderate and severe sleep apnea. In addition, correlation analyses for accuracy measures between CRM and NightOwl™ will be conducted along with patient ease-of-use and satisfaction questionnaires.

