## Objectives and hypothesis

To use a home-monitoring device NightOwl™ to screen patients with AF for sleep apnea and thus;Report the prevalence and severity of sleep apnea in patients with AF.Assess the accuracy, user-experience, and feasibility of home-screening for sleep apnea in patients with AF.

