### Study design

The is a cross sectional study. In total two visits will be planned, with a third visit for the first 20 participants and participants with AHI > 15 included in the study (Fig. 1).Initial visit with time for clinical evaluation, questionnaire of OSA symptoms, the participant borrows a NightOwl™ and receive device instructions.Four night of recording with NightOwl™ in home environment.Follow-up visit for the home-monitoring results and soft node questionnaire.For the 20 first patients and for all patients where the home test is showing (AHI > 15) a fourth visit at the sleep apnea clinic will be arranged.

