### Statistical analysis

The prevalence will be calculated by the proportion of participants with sleep apnea out of all participating individuals. The differences between patients with and without a diagnosis of sleep apnea (i.e. AHI > 5) will be assessed by the independent sample t test for continuous variables and the χ2 test for categorical variables. For the participants undergoing CRM, accuracy measurements of the home-monitoring of the NightOwl™ will be conducted by correlation analyses including scatter plots based on AHI measured by CRM versus AHI measured by NightOwl™ and receiver operator characteristics (ROC) with area under the curve (AUC) values.

As an exploratory analysis, a multivariate logistic regression analysis will be performed to test the predictors of a set of factors to detect the presence of any sleep apnea and presence of severe sleep apnea. These include age, body mass index (BMI), sex, neck circumference, European Heart Rhythm Association (EHRA) score (0–4), type of AF (new AF, paroxysmal, persistent AF, permanent AF), prior treatment for AF, blood samples, echocardiographic data and electrocardiogram data. Similar analysis using a multivariate logistic regression will evaluate if commonly used sleep apnea questionnaire can predict presence of sleep apnea in these patients. Correlation analyses will also be conducted of the clinical feasibility questionnaires.

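### NightOwl accuracy is to be computed on everyone who gets CRM, but after the first 20 participants only those with screening AHI > 15 get it, so correlation and ROC/AUC carry a modest partial-verification bias

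*Protocol article*

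**What the plan says.** The Cardiorespiratory monitoring section defines who gets the reference test: "The CRM for the 20 first participants and for the participants where the home test is showing" an AHI above 15. The Abstract (Methods) and Study design give the same rule. The device section says that the four home nights are presented as averages, so the reading that triggers referral is the four-night screening AHI.

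The Statistical analysis section fixes the accuracy set and the statistics: "For the participants undergoing CRM, accuracy measurements of the home-monitoring of the NightOwl™ will be conducted by correlation analyses including scatter plots", together with "receiver operator characteristics (ROC) with area under the curve (AUC) values". It does not separate the two routes into CRM and applies no weights.

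The Cardiorespiratory monitoring section also says which NightOwl reading is paired with CRM: "Simultaneously with undergoing the CRM, the participants will also be assessed by the NightOwl™ the same night".

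The target population is set under Objectives and hypothesis: "Assess the accuracy, user-experience, and feasibility of home-screening for sleep apnea in patients with AF". The limitations (Abstract, Strengths and limitations, Discussion) cover recruitment from one clinic, the absence of polysomnography, central versus obstructive events, and unrecorded data. They do not mention that access to the reference test depends on the home-test result.

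**The concern.** Everyone with screening AHI above 15 is verified. A participant at or below 15 is verified only if among the first 20 enrolled. The set that undergoes CRM is therefore enriched for high NightOwl readings, and accuracy measures computed on it do not directly estimate accuracy in AF patients at large.

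At the AHI 15 threshold, the verified participants without disease include too many with high readings. That lowers specificity and AUC, while unverified missed cases raise apparent sensitivity. At the AHI 5 threshold, which the protocol uses to define sleep apnea, the verified cases are disproportionately severe and easy to detect, so AUC rises. For a screening device the important error is the missed case, and those are seen almost only among the first 20.

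**Working it through.** **The plan's own figure.** The article gives no figure for the accuracy analysis. Its one calculated sample size, 113, concerns the prevalence of severe sleep apnea (10% against 4%). It reproduces as a two-sided one-sample test: ((1.960·√(0.04·0.96) + 0.842·√(0.10·0.90))/0.06)² = 112.6, rounded up to 113. It has no bearing on this point.

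**Step 1: how many are verified.** From the document: N = 150, the first 20 always verified, cut-off AHI > 15. The share q above 15 is an assumption. Verified screen-positives = 150q; verified screen-negatives = 20(1−q); all screen-negatives = 150(1−q).

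| q | CRM total | screen-positive share of CRM set | screen-negatives verified |
|---|---|---|---|
| 20% | 30 + 16 = 46 | 65% | 16 of 120 |
| 30% | 45 + 14 = 59 | 76% | 14 of 105 |
| 40% | 60 + 12 = 72 | 83% | 12 of 90 |
| 50% | 75 + 10 = 85 | 88% | 10 of 75 |

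In every row 20/150 = 13% of screen-negatives are verified, against 100% of screen-positives.

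**Step 2: effect on the planned same-night comparison.** This was simulated with 2,000 replicates of 150 patients per scenario. Each patient has a log-normal underlying AHI. Night-to-night variation, CRM error and NightOwl error are added on the log scale. Referral uses the mean of four NightOwl nights, and accuracy uses CRM and NightOwl on one further shared night. All inputs are assumptions, because the document supplies none:

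- A: median 5, log-SD 0.9; SDs for night 0.30, CRM 0.25, NightOwl 0.35
- B: as A, median 10
- C: as A, median 12, log-SD 0.8
- D: median 10, log-SD 0.9; SDs for night 0.40, CRM 0.40, NightOwl 0.50

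Each cell shows all 150, then the pooled CRM set:

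| | A | B | C | D |
|---|---|---|---|---|
| Share with screening AHI > 15 | 14% | 36% | 43% | 39% |
| AUC, CRM AHI ≥ 15 | 0.961→0.940 | 0.946→0.917 | 0.933→0.904 | 0.902→0.867 |
| AUC, CRM AHI ≥ 5 | 0.943→0.974 | 0.951→0.982 | 0.948→0.979 | 0.907→0.935 |
| Sensitivity at 15 | 0.743→0.814 | 0.819→0.866 | 0.822→0.865 | 0.757→0.813 |
| Specificity at 15 | 0.953→0.887 | 0.901→0.789 | 0.873→0.754 | 0.860→0.740 |
| Correlation of log AHI | 0.907→0.921 | 0.907→0.882 | 0.887→0.852 | 0.826→0.785 |

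Sensitivity and specificity are not named in the plan, but they are the coordinates of the ROC curve. A second simulation gave somewhat smaller shifts: AUC about −0.02 at 15 and +0.02 at 5, sensitivity at 15 up about 0.03, specificity at 15 down 0.08-0.09, correlation down 0.01-0.02. The ranges in the conclusion cover both.

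**Step 3: does the unselected part recover the target?** AUC at 15 in the first 20 alone averaged 0.961, 0.947, 0.933 and 0.900 in scenarios A to D, against 0.961, 0.946, 0.933 and 0.902 in all 150. The simulation draws the first 20 from the same population as later patients, so this agreement rests on that assumption.

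**Step 4: how thin the low side is.** In the pooled set a verified screen-negative would carry weight 105/14 = 7.5 at q = 30% (and 7.5 in every row of Step 1). As an illustration, take true sensitivity 0.80 and specificity 0.90 for the screening result. Prevalence is then (0.30 − 0.10)/(0.80 − 0.10) = 0.286, and false negatives number 150 × 0.286 × 0.20 = 8.6. Of these, 8.6 × 20/150, or about 1, is verified.

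**The case against.** The strongest defence is the repeated NightOwl reading. The comparison uses the CRM night and not the reading that triggered referral, which weakens the selection. This stands, and it is why the shifts in Step 2 are modest. It does not remove them, because the two readings are correlated.

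The analysis is also expressly limited to participants undergoing CRM. A reader might infer that the authors treat this set as representative of AF patients. The article does not say so; it only omits weights, separate reporting and a caveat. Such detail could sit in a fuller document, but the article does state the analysis set and the statistics, and as stated they do not match the objective.

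Three stronger readings are tempting and are not supported:

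- **A large bias at AHI 15.** If the four-night screening result were the test under evaluation, an assumed sensitivity of 0.80 would appear as 0.80/(0.80 + 0.20 × 0.133) = 0.97, and a specificity of 0.90 as (0.90 × 0.133)/(0.90 × 0.133 + 0.10) = 0.55. The protocol bases the comparison on the simultaneous night, so these are not the effects on the planned analysis.
- **A marked loss of correlation.** Restricting to AHI > 15 alone would lower the correlation more, but the planned set includes the first 20. In the pooled set the change is small and can go either way.
- **A uniformly flattering or uniformly harsh result.** The direction depends on the threshold and the statistic.

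Finally, the NightOwl-CRM comparison is listed among other outcomes of interest. The primary prevalence estimate, the predictor analysis using NightOwl-defined apnea and the sample size do not depend on it.

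**Conclusion.** The point holds. As written, the accuracy analysis is subject to partial-verification bias when read as accuracy in AF patients. Across the assumed AHI distributions and errors:

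- AUC at AHI 15 falls by about 0.02-0.035; at AHI 5 it rises by about 0.02-0.03.
- Sensitivity at 15 rises by about 0.03-0.07; specificity at 15 falls by about 0.07-0.12.
- Pooled correlation changes by about −0.04 to +0.01.

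These sizes are conditional on inputs that the document does not give. The selection rule and the pooled set are explicit. Because accuracy is a stated objective and part of the hypothesis, this should be fixed. It does not undermine the study or its primary outcome.

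**What to change.** In the Statistical analysis section:

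1. Report correlation and ROC/AUC separately in the first 20 consecutive participants, as the estimate unselected by the screening result.
2. For the pooled CRM set, add weighted estimates. Base the weights on the four-night screening AHI, not on the CRM-night reading: weight 1 if above 15; number of screen-negatives divided by number of verified screen-negatives if 15 or below. State that this assumes the first 20 are exchangeable with later enrollees. The weights are not strictly known by design, since a screen-negative enrolled after participant 20 has no chance of CRM.
3. Label unweighted pooled results as applying to the CRM-referred sample.

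In the Discussion, name partial verification as a limitation.

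The cost is a few sentences and a few lines of code, with no change to who receives CRM. The drawback is precision. The first 20 alone are few, and the low-AHI side of the weighted analysis rests on about 10-16 patients with very few false negatives, so intervals will be wide and bootstrap intervals may be unstable. The report should say so.

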### Statistical analysis

The prevalence will be calculated by the proportion of participants with sleep apnea out of all participating individuals. The differences between patients with and without a diagnosis of sleep apnea (i.e. AHI > 5) will be assessed by the independent sample t test for continuous variables and the χ2 test for categorical variables. For the participants undergoing CRM, accuracy measurements of the home-monitoring of the NightOwl™ will be conducted by correlation analyses including scatter plots based on AHI measured by CRM versus AHI measured by NightOwl™ and receiver operator characteristics (ROC) with area under the curve (AUC) values.

As an exploratory analysis, a multivariate logistic regression analysis will be performed to test the predictors of a set of factors to detect the presence of any sleep apnea and presence of severe sleep apnea. These include age, body mass index (BMI), sex, neck circumference, European Heart Rhythm Association (EHRA) score (0–4), type of AF (new AF, paroxysmal, persistent AF, permanent AF), prior treatment for AF, blood samples, echocardiographic data and electrocardiogram data. Similar analysis using a multivariate logistic regression will evaluate if commonly used sleep apnea questionnaire can predict presence of sleep apnea in these patients. Correlation analyses will also be conducted of the clinical feasibility questionnaires.

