### Outcomes

The primary outcome of the study is the prevalence with 95% confidence intervals of sleep apnea in patients with AF detected by NightOwl™. This analysis will be total and stratified by severity of sleep apnea.

The secondary outcome will be an exploratory analysis of predictors of sleep apnea and predictors of moderate and severe sleep apnea in the participants using baseline characteristics and clinical data of the participants.

Other outcomes of interest are;The correlation between NightOwl™ and CRM diagnostic testing for sleep apnea and the correlation between sleep apnea screening questionnaire for CRM and NightOwl™.Evaluation of user-experience and compliance with NightOwl™.The evaluation of user-experience and compliance will consist of a survey questionnaire build with help from CATCHET Unified Method for Assessment of Clinical Feasibility (CUMACF) [21]. The purpose of this method is to deliver a standardized way of measuring clinical feasibility of the many new technologies being designed and tested. The clinical feasibility questionnaire is divided into three parts: Usage Adoption, Perceived Usefulness and Usability, and Health Efficacy.Inter-variability of NightOwl™ recordings.Recordings of four nights will be used to assess any inter-variability between the NightOwl™ recording. Furthermore, the four nights recording can clarify potential night-to-night fluctuations and thereby gives a more precise screening of the presence of sleep apnea.

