**Fig. 3 Fig3:**
[figure not shown]
NightOwl™ Data Output (sample). The NightOwl™ derives all parameters sufficient to diagnose sleep apnea

The product complies with Medical Device Directive 93/42/ECC and amendments 2007/47/EC requirements. The product is CE marked i.e. the product is authorized for clinical use. Instructions of use and complete product description can be found at http://www.ectosense.com/eifu.

Data captured from NightOwl™ comprises data from four sleep evaluations and consists of the parameters AHI, ODI, heart rate and sleep time. The AHI is graded into four different classifications, them being without sleep apnea (AHI < 5), mild sleep apnea (5 < 15), moderate sleep apnea (15 < 30) and severe sleep apnea (> 30). Thus, NightOwl™ defines sleep apnea as AHI > 5. The data captured from the four nights is to be presented in average quantities thereby counteracting potentially variations in the participants’ sleep data from night to night.

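### NightOwl accuracy against CRM is to be judged by correlation and AUC, which do not estimate systematic over- or under-reading of AHI, although the primary outcome depends on fixed AHI cut-offs

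*Protocol article*

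**What the plan says.** All references are to the protocol article.

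- **Objectives and hypothesis** makes accuracy an aim: "Assess the accuracy, user-experience, and feasibility of home-screening for sleep apnea in patients with AF". The hypothesis adds that NightOwl is an accurate test.
- **Statistical analysis** fixes how accuracy is measured in participants who undergo CRM: "correlation analyses including scatter plots based on AHI measured by CRM versus AHI measured by NightOwl™", together with "receiver operator characteristics (ROC) with area under the curve (AUC) values".
- The other places that describe the comparison speak only of correlation. The abstract's Methods say "correlation analyses for accuracy measures between CRM and NightOwl™ will be conducted", Outcomes lists "The correlation between NightOwl™ and CRM diagnostic testing for sleep apnea", and Cardiorespiratory monitoring says the simultaneous recording "allows for a direct analysis of the correlation of AHI (and other parameters) measured by CRM and NightOwl™".
- **Outcomes** defines the primary outcome as the "prevalence with 95% confidence intervals of sleep apnea in patients with AF detected by NightOwl™", in total and by severity.
- **The device** (text after Fig. 3) sets the classes at AHI 5, 15 and 30: "Thus, NightOwl™ defines sleep apnea as AHI > 5".
- **Study design** and **Cardiorespiratory monitoring** restrict CRM to the first 20 participants and those whose home test shows AHI > 15.

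The article names no mean difference, limits of agreement, concordance coefficient or kappa, and no sensitivity or specificity at a stated cut-off.

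**The concern.** Correlation and AUC measure whether two devices rank patients alike. The primary outcome needs something else: that NightOwl's AHI be right on the absolute scale near 5, 15 and 30. A device that reads consistently high or low can rank patients very well and still put many of them in the wrong class.

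The claim at stake is that NightOwl is accurate. If it rests on a high r or AUC, it says nothing about whether the reported prevalence and severity distribution are shifted. Correlation has a second weakness here. It depends on the spread of AHI in the sample, and that spread is partly set by the CRM referral rule.

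**Working it through.** **1. The plan's own figure.** The only computed figure is the sample size of 113 (Power calculations: 10% against 4%, alpha 0.05, power 80%). A two-sided one-sample test of a proportion gives

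n = [1.960·√(0.04·0.96) + 0.842·√(0.10·0.90)]² / 0.06² = 112.56, rounded up to 113.

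It reproduces. The present point does not depend on it.

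**2. What r and AUC respond to.** Write NightOwl AHI as N and CRM AHI as C. For any a and any b > 0, corr(C, a + bN) = corr(C, N). Spearman's rho and AUC use only ranks, so any increasing transformation of N leaves them unchanged. This needs no assumption about the data.

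**3. What the cut-offs respond to.** Assumptions not in the documents: CRM AHI is log-normal with median 8 and log-SD 1, and NightOwl reads k times CRM without random error. Then P(N > c) = Φ(ln(8k/c)).

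| Cut-off c | k = 1 | k = 1.25 | k = 1.5 | Shift at 1.25 | Shift at 1.5 |
|---|---|---|---|---|---|
| 5 | 68.1% | 75.6% | 80.9% | 7.5 | 12.8 |
| 15 | 26.5% | 34.3% | 41.2% | 7.8 | 14.7 |
| 30 | 9.3% | 13.6% | 18.0% | 4.3 | 8.7 |

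Shifts are in percentage points. In every column r (on the AHI scale) and AUC equal 1, because random error is assumed away.

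**4. Comparison with sampling error.** The 95% half-width is 1.96·√(p(1−p)/N). At N = 150 it is 7.5 points for p = 68.1%, 7.1 for 26.5% and 4.7 for 9.3%. Shifts at 1.25 times are therefore about as large as the half-widths, and shifts at 1.5 times are clearly larger.

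**5. A second set of assumptions, with random error.** Here 200,000 pairs were simulated with median AHI 5 (to match the article's hypothesis of around 50%), log-SD 0.9 or 1.4, and NightOwl log-error SD 0.3.

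| NightOwl reads | r (log-SD 0.9 / 1.4) | AUC at CRM AHI > 5 | NightOwl prevalence of AHI > 5 | Specificity at 5 |
|---|---|---|---|---|
| no bias | 0.924 / 0.951 | 0.968 / 0.986 | 50% / 50% | 0.90 / 0.93 |
| × 1.5 | 0.924 / 0.951 | 0.968 / 0.986 | 66% / 61% | 0.66 / 0.77 |
| × 0.67 | 0.924 / 0.951 | 0.968 / 0.986 | 33% / 39% | 0.99 / 0.99 |

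The accuracy statistics named in the plan are identical in all three rows. Those it does not name do move. At × 1.5 the mean difference is +4.2 (log-SD 0.9) or +7.6 (log-SD 1.4) events/h and specificity falls. At × 0.67 the mean difference is −2.3 or −4.0 and sensitivity falls from 0.90 / 0.93 to 0.66 / 0.77.

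**The case against.** **The plan is not blind to bias.** A reader might infer that nothing planned could reveal a systematic error. The article does not support that. A scatter plot of two AHI readings in the same units can show an offset or a steeper slope by eye, and an ROC curve contains the sensitivity and specificity at NightOwl values of 5, 15 and 30. This stands. But the article commits to neither an identity line nor those operating points, and a plot gives no estimate or interval.

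**The size is assumed.** A reader might also infer that NightOwl is biased or that the prevalence will be wrong. Nothing in the article shows this; the Background calls the single-night validation against polysomnography promising. The AHI distributions and multipliers are assumptions, and the median of 8 implies 68% prevalence against the article's hypothesis of around 50%. This stands for the size of the shift. It does not touch the invariance in step 2.

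**Accuracy is not primary.** The abstract makes it secondary, and Outcomes lists the CRM comparison among other outcomes of interest. The primary outcome is defined as detected by NightOwl, so its value would not change with the accuracy statistic; only its interpretation would. The article also admits a higher risk of false positives and negatives without polysomnography. This lowers the priority but does not remove the point.

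**The usual remedies have limits here.** An intraclass or concordance coefficient depends on AHI spread as r does, and kappa depends on the class mix. Beyond the first 20, CRM follows only a home AHI > 15, so naive sensitivity and specificity carry partial-verification bias. This stands and shapes the fix.

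**A fuller plan may exist.** An article may leave detail to another document. Here it names the method in its statistical section and speaks of correlation in three other places, so the issue is a stated choice rather than an omission.

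**Conclusion.** The concern holds in a limited form. The statistics named for accuracy, r and AUC, do not estimate systematic over- or under-reading of AHI, and the scatter plot shows it only informally. Because prevalence and severity are defined at fixed AHI values, a high r or AUC would not support calling NightOwl accurate for them.

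The invariance is exact. The size is illustrative. Under the median-8 assumption, a 1.5-fold over-reading shifts prevalence by about 13, 15 and 9 points at the three cut-offs. A 1.25-fold over-reading shifts it by amounts close to the confidence-interval half-widths at N = 150. It would be wrong to say that the plan cannot reveal bias or that the device is known to have any. Since accuracy is a secondary aim and the paired data are already to be collected, this should be fixed but does not threaten the design.

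**What to change.** 1. Make agreement on the same-night CRM and NightOwl pairs the main accuracy analysis: Bland-Altman mean difference with 95% limits of agreement, and confidence intervals for both. If the spread of differences grows with AHI, use log-AHI and report a ratio.
2. Cross-classify same-night NightOwl against CRM at 5, 15 and 30.
3. Report sensitivity and specificity, including those of the four-night mean that feeds the primary outcome, separately for the unselected first 20 participants, or corrected for referral at home AHI > 15.
4. If an intraclass coefficient or kappa is given, state that it depends on the referred sample.
5. Keep correlation, scatter plots (with an identity line) and AUC as descriptive.

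The cost is changed wording and a little more analysis, with no new patients, visits or recordings. The drawback is imprecision in the first 20. At the hypothesised prevalence of around 50%, about 10 of them would have CRM AHI > 5, so one misclassified patient moves sensitivity by 10 points. Information near AHI 5 will come mainly from this group, and the intervals should be shown.

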### **Hypothesis**

In patients with AF, the prevalence of unrecognized OSA is high (around 50%) and home-monitoring test using NightOwl™ is a viable, easy, and accurate test of measuring sleep apnea.

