### Power calculations

Assuming a prevalence of severe sleep apnea of 10% in the population compared to 4% in the general population, with alpha 0.05 and a power of 80% a sample size of 113 was calculated. We plan to include 150 patients due to drop-outs, and potentially difficulties of patients applying the device.

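### The predictor models use the four-night mean AHI only after cutting it; one added model on the continuous value would be a cheap gain in precision

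*Protocol article*

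**What the plan says.** Under The device (text after Fig. 3), AHI is recorded on four nights and "The data captured from the four nights is to be presented in average quantities". The same text grades it at 5, 15 and 30.

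Under Outcomes, "The secondary outcome will be an exploratory analysis of predictors of sleep apnea and predictors of moderate and severe sleep apnea", using baseline and clinical data.

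Under Statistical analysis, three pieces of work relate baseline data to sleep apnea:

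- Group comparisons: "The differences between patients with and without a diagnosis of sleep apnea (i.e. AHI > 5) will be assessed by the independent sample t test". This applies to continuous variables; categorical ones get the chi-square test.
- Regression: "a multivariate logistic regression analysis will be performed to test the predictors of a set of factors to detect the presence of any sleep apnea", with a second outcome of severe sleep apnea.
- Questionnaires: a similar logistic analysis.

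No model with continuous or ordinal AHI as the outcome is described for baseline predictors. The numerical AHI is used elsewhere, in the scatter plots and correlations of NightOwl against cardiorespiratory monitoring.

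**The concern.** Cutting AHI is necessary to report a prevalence. It is not necessary to learn which characteristics go with more sleep apnea. In the first model a participant with AHI 6 counts the same as one with AHI 60. In the second, AHI 1 counts the same as AHI 29, and at the planning figure about 90% of participants fall into one undifferentiated group.

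With at most about 150 participants, real predictors may be missed, and the two binary models may name different predictors simply because they discard different amounts of information. The Discussion hopes to identify important predictors and the Conclusion speaks of informing guidelines on them, so this bears on a stated aim, though not on the primary one.

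**Working it through.** **1. The plan's own sample size.** Power calculations states: "Assuming a prevalence of severe sleep apnea of 10% in the population compared to 4% in the general population", and "with alpha 0.05 and a power of 80% a sample size of 113 was calculated". A two-sided one-sample test of a proportion reproduces it:

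n = [1.960·√(0.04·0.96) + 0.842·√(0.10·0.90)]² / 0.06² = 112.56, so 113.

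This concerns the prevalence of severe disease only. No power is stated for the predictor analysis.

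**2. Inputs for the check.**

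- Any sleep apnea, 0.50: Hypothesis ("the prevalence of unrecognized OSA is high (around 50" per cent).
- Severe, 0.10: Power calculations.
- Number analysed, 113 to 150: Power calculations ("We plan to include 150 patients due to drop-outs").
- Alternative prevalences, 0.85 any and 0.28 severe: the 100-patient AF study cited in Background.
- **Assumed, not in the documents:** log AHI is normal; one continuous predictor has correlation r with it; tests are two-sided at 5%.

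The 50% and 10% figures fix the distribution: mean log AHI = ln 5 and SD = (ln 30 − ln 5)/1.2816 = 1.398. This implies P(AHI > 15) = 0.216.

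**3. Information kept by a cut.** For a modest effect, a cut leaving a proportion p above it retains E = φ(z_p)² / [p(1 − p)], where φ is the normal density and z_p the normal quantile at the cut.

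| Cut | p | E |
|---|---|---|
| AHI 5 | 0.50 | 0.159/0.25 = 0.637 |
| AHI 15 | 0.216 | 0.507 |
| AHI 30 | 0.10 | 0.0308/0.09 = 0.342 |
| AHI 5, cited study | 0.85 | 0.426 |
| AHI 30, cited study | 0.28 | 0.562 |

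If the continuous model has 80% power, the cut model has about Φ(√E·(1.960 + 0.842) − 1.960). That is 60.8% at p = 0.50 (loss 19 points) and 37.4% at p = 0.10 (loss 43 points).

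**4. Simulation.** 20,000 trials per setting, linear regression on log AHI against univariable logistic regression (likelihood-ratio test):

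| n | r | Linear power | Loss at AHI 5 (p = 0.50) | Loss at AHI 30 (p = 0.10) | Loss at AHI 5 (p = 0.85) | Loss at AHI 30 (p = 0.28) |
|---|---|---|---|---|---|---|
| 113 | 0.20 | 56.9% | 16.1 | 32.7 | 27.8 | 20.1 |
| 113 | 0.25 | 76.7% | 18.9 | 42.6 | 34.6 | 25.1 |
| 113 | 0.30 | 90.1% | 16.5 | 43.5 | 34.7 | 22.3 |
| 150 | 0.20 | 68.8% | 18.9 | 39.1 | 32.5 | 23.4 |
| 150 | 0.25 | 87.4% | 17.4 | 43.5 | 35.2 | 22.7 |
| 150 | 0.30 | 96.4% | 11.1 | 38.9 | 27.9 | 16.1 |

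At the plan's prevalences the losses are 11 to 19 points at AHI 5 and 33 to 44 at AHI 30. A separate simulation of the same settings gave 11 to 19 and 35 to 45, and 21 to 29 at AHI 15. I therefore quote 33 to 45 for the severe cut.

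**5. How far the figures move.** Widening r to 0.15–0.35 gives about 5 to 19 points at AHI 5 and 19 to 44 at AHI 30. Over that wider range, the cited study's prevalences give about 17 to 35 and 8 to 25. The gap is not bought with type I error: null rejection rates at n = 150 were 5.5% (linear), 4.5% (AHI 5) and 5.6% (AHI 30).

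**6. The second cut.** Outcomes names moderate and severe disease, as does the Abstract. Statistical analysis names severe only. The two imply different cuts and different losses.

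**The case against.** The strongest case for the plan is that logistic regression answers the question it poses. Outcomes and Statistical analysis ask about the presence of sleep apnea, and the Discussion wants tools that identify patients. A ratio of AHI gives no probability of disease. The analysis is labelled exploratory in both sections and has no power target. The simulation also draws its data from the model it favours. All of this stands. It is why the logistic models should not be demoted and why the severity is low.

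Three stronger readings are tempting, and the documents do not support them:

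- *That the secondary outcome loses a definite number of points.* The plan states neither an effect size nor an AHI distribution. With the 85% and 28% prevalences it also cites, the loss grows at AHI 5 and shrinks at AHI 30.
- *That the loss at AHI 30 is the loss for the secondary outcome.* As defined under Outcomes, that outcome includes moderate disease, where the loss is smaller.
- *That AHI is dichotomised everywhere.* Outcomes also plans a correlation of the screening questionnaires with NightOwl and cardiorespiratory monitoring, and nothing says that AHI is cut there.

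What the objection does not remove is that a loss appears in every setting examined, and that avoiding it needs no new data.

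**Conclusion.** A cheap improvement, not an error in the plan. Each predictor regression described discards part of a measurement already in hand. If log AHI is normal with 50% above 5 and 10% above 30, and a predictor has correlation 0.20 to 0.30, the cost at 113 to 150 participants is about 11 to 19 points of power at AHI 5, 21 to 29 at AHI 15 and 33 to 45 at AHI 30. The direction is robust; the size depends on inputs the plan does not give.

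The figures are for a single predictor. At 10% severe, 113 to 150 participants yield about 11 to 15 events (0.10·113 = 11.3; 0.10·150 = 15) for ten listed factors or groups of factors, so the multivariable severe model would be weaker still.

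**What to change.** In Statistical analysis:

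1. Keep the planned logistic models for the presence-of-disease question.
2. Add alongside them one pre-specified model of the same predictors on the continuous four-night mean AHI: linear regression on log(AHI + 1), which retained nearly all the power of the log AHI model in simulation. If residuals are poor, use an ordinal cumulative-probability model instead. From the linear model, report the AHI ratio per predictor with its 95% confidence interval.
3. Reconcile the second cut between Outcomes (moderate and severe) and Statistical analysis (severe).

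The cost is one paragraph of wording, one extra model with a fit check, and a second effect scale to report. No new participants, visits or measurements are needed, and the primary prevalence outcome is unchanged.
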